**Methods/Design:**

*Study design*: An observational, longitudinal, prospective cohort study, undertaken in the Region of Valencia, with an initial follow-up period of five years; *Subjects*: 14,500 men and women over the age of 50, residing in the Region and receiving healthcare from centers where the ABUCASIS electronic clinical records system is implanted; *Sources of data*: The ABUCASIS electronic clinical record system, complemented with hospital morbidity registers, hospital Accidents & Emergency records and the Regional Ministry of Health's mortality register; *Measurement of results*: Incident osteoporotic fracture (in the hip and/or major osteoporotic fracture) during the study's follow-up period. Independent variables include clinical data and complementary examinations; *Analysis*: 1) Descriptive analysis of the cohorts' baseline data; 2) Upon completion of the follow-up period, analysis of the strength of association between the risk factors and the incidence of osteoporotic fracture using Cox's proportional hazards model; 3) Development and validation of a model to predict risk of osteoporotic fracture; the validated model will serve to develop a simplified scale that can be used during routine clinical visits.

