## Methods/Design

### Main objective

To develop and validate a risk prediction scale for osteoporotic fracture in the adult population of the Region of Valencia, Spain.

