### Specific objectives

1. To describe baseline characteristics of the cohort under study and the prevalence of risk factors for osteoporosis. This objective will reveal the current prevalence of risk factors for osteoporosis in men and women over 50 years in the Region of Valencia.

2. To evaluate the strength of association between risk factors and the incidence of osteoporotic fracture at five years for the overall population over the age of 50, and for the five-year age-sex subgroups. This objective will also be developed specifically for the risk of hip fracture.

3. To analyze using survival models the time relationship between risk factors and the incidence of osteoporotic fracture and the risk of hip fracture.

4. To identify in patients with osteoporotic and hip fracture factors of poor prognostic for survival.

5. To develop and validate a prediction scale for the risk of osteoporotic fracture at five years, specific to the population of the Region of Valencia, Spain.

6. To evaluate the calibration and the discrimination capacity of the FRAX scale in the population of the Region of Valencia and, if necessary, to recalibrate this scale for its use in the Valencia population.

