### Statistical analysis

Once the recruiting process has been completed, the cohort baseline data will be analyzed. A description will be made of the patients' characteristics along with their current risk factors. The analysis will be stratified by five-year age-sex subgroups. The appropriate parameters (means, proportions) will be used with each variable with their corresponding 95% confidence intervals (CI95%). A bi-variable analysis will also be made to evaluate the relationships between risk factors that are of most interest. Simple Odds Ratios (OR) will be applied to estimate the strength of association and, when necessary, multiple logistic regression models will be used.

At two and five years of follow-up, an analysis will be made of the strength of association between the risk factors and the incidence of osteoporotic fracture in all locations and in the hip. For this, bi-variable analysis and Cox' proportional hazards models will be used. Additionally, a specific model will be developed to analyze the probability of death once a fracture has occurred (controlling for the effect of the different types of fractures).

Next, the most parsimonious of Cox' proportional hazards models will be applied to two-thirds of the sample (approximately 10,000 subjects randomly selected) to develop a scale to predict the risk of osteoporotic fracture. The scale's prediction capacity will be evaluated with the C statistic, and its calibration will be evaluated with the Hosmer-Lemeshow test, or a similar test. The predictive weights of the risk factors obtained in this model will be applied to the remaining third of the database (approximately 5,000 subjects) to evaluate whether prediction capacity (C statistic > 0.75) and calibration (non-significant Hosmer-Lemeshow test) are maintained. Scaling techniques will then be applied to construct a simplified scale on the basis of the validated model.

Finally, the calibration and the capacity for discrimination of the FRAX scale will be evaluated in the population of the Region of Valencia, Spain. If necessary, the FRAX will be recalibrated to make it more appropriate for the population in question. This time, the weights of the original scale will be used in conjunction with the incidence of osteoporotic fracture derived from our study. If the scale shows poor prediction capacity (statistics < 0,75), or if it is not correctly calibrated, it will be recalibrated with the weights derived from our own scale.

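### The simplified scale meant for clinic use is built after validation, and the plan states no check of its own discrimination or calibration

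*Protocol article*

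**What the plan says.** The Main objective is "To develop and validate a risk prediction scale for osteoporotic fracture in the adult population of the Region of Valencia, Spain". Specific objective 5 repeats this for five-year risk.

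The Statistical analysis section then sets out four steps:

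1. The most parsimonious Cox model "will be applied to two-thirds of the sample (approximately 10,000 subjects randomly selected) to develop a scale to predict the risk of osteoporotic fracture". Its C statistic and calibration are assessed.
2. For validation, "The predictive weights of the risk factors obtained in this model will be applied to the remaining third of the database (approximately 5,000 subjects", to see whether "prediction capacity (C statistic > 0.75) and calibration (non-significant Hosmer-Lemeshow test) are maintained".
3. After that, "Scaling techniques will then be applied to construct a simplified scale on the basis of the validated model".
4. The plan then turns to another instrument: "Finally, the calibration and the capacity for discrimination of the FRAX scale will be evaluated in the population of the Region of Valencia, Spain".

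The Methods/Design paragraph of the abstract has the same order and says who the simplified version is for: "the validated model will serve to develop a simplified scale that can be used during routine clinical visits".

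**The concern.** The performance criteria in step 2 apply to the Cox weights. The simplified scale of step 3 does not exist at that point, and no later step measures how well it ranks patients or how closely its predicted risks match observed ones.

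Turning a Cox model into points usually means rounding coefficients and cutting continuous variables such as age into bands. Patients whom the model separates can then receive the same score, and the order of others can change. The absolute risk attached to each score also has to be assigned anew. A result obtained for the model is therefore indirect evidence about the scale.

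This matters because the article expects the scale to support treatment decisions through intervention thresholds. A threshold acts on absolute risk, so the calibration of the version in use is what counts.

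**Working it through.** **Sequence.** The point rests on the order of steps, not on a disputed figure.

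| Object | Built | Tested in held-out third | Stated use |
|---|---|---|---|
| Full-weight Cox score | Step 1, in two-thirds | Yes, step 2 | Basis for the simplified scale |
| Simplified scale | Step 3, after step 2 | No step stated | Routine clinical visits (abstract) |
| FRAX | Existing | Evaluated in step 4 | Comparison, recalibration if needed |

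**How much C could change.** The document gives no coefficients and no scaling method, so any figure needs assumptions. Two simulations were run, both at an event risk of 1.5%, the plan's five-year hip fracture incidence.

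*Simulation A* (assumed: 400,000 people aged 50 to 95, log hazard ratio 0.10 per year of age, six binary risk factors). The full-weight C is 0.808.
- Points rounded in units of ln(1.5), ten-year age bands: 0.797, a loss of 0.011.
- One point per item: 0.782, a loss of 0.026.

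Both simplified versions stay above 0.75.

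*Simulation B* (assumed: 500,000 people, a logistic model with age and one other continuous predictor, both standard normal, and four binary factors, under three sets of coefficients). The banded score uses five age bands, cuts the other continuous predictor in two and gives one point per binary factor. The cruder score also cuts age in two.

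| Full-weight C | Banded score (loss) | Cruder score (loss) |
|---|---|---|
| 0.701 | 0.685 (0.016) | 0.653 (0.048) |
| 0.739 | 0.720 (0.019) | 0.670 (0.069) |
| 0.787 | 0.759 (0.028) | 0.698 (0.089) |

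In the first two rows the model itself is below 0.75. Only in the third row does the model pass and a derived score fail, and only the cruder score fails.

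**Loss of resolution within an age band.** At the assumed log hazard ratio of 0.10 per year, the last and first years of a ten-year band differ by a hazard ratio of exp(0.10 × 9) = 2.46. Simulated risk ratios were 2.39 (ages 70 to 79) and 2.41 (80 to 89). For a five-year band the figure is exp(0.10 × 4) = 1.49. These ratios follow directly from the assumed coefficient and are not a finding about this cohort.

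**What the held-out third can show.** First, the plan's sample size, from Population and sample, with two-sided alpha 0.05, power 0.80, SD 0.75, hazard ratio 1.33, R² 0.10, incidence 0.015 and 10% losses:
- Events: (1.960 + 0.842)² / (0.75² × ln(1.33)² × 0.90) = 190.6.
- N: 190.6 / 0.015 / 0.90 = 14,121.3, rounded up to 14,122. This matches the plan.

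The held-out third is then 14,122 / 3 = about 4,707 people, with 14,122 × 0.90 × 0.015 / 3 = about 64 hip fractures (60 if the plan's stated total of 180 is used). At C = 0.75 the Hanley-McNeil standard error is about 0.036 with 64 events (0.037 with 60), so the 95% interval is about 0.68 to 0.82 either way. The same people can be scored with both versions at no cost in sample size. The article describes fractures at other sites as much more frequent than hip fracture, so the main endpoint should give more events, but no rate is stated.

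**The case against.** Four objections carry weight.

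- **The objective may already be met.** A reader might infer that the main objective fails. The document does not support that: the Statistical analysis section also calls the full-weight Cox score a scale, and that score is developed and tested. What remains is that the abstract assigns clinic use to the simplified version, which is not tested.
- **Nobody calls the simplified scale validated.** A reader might also infer that the published tool would carry that label without evidence. The article applies the word only to the model, so this would be speculation. It is likewise unsupported to say that risks shift most where treatment thresholds would lie: no threshold is given, and the Discussion links treatment criteria to further cost-utility research.
- **A journal article condenses.** A fuller plan could add the check, and nothing in the article forbids it. Points derived mechanically from locked weights could still be scored in the held-out third. This limits the point to the document at hand but does not remove it, because the article states the order outright in two places, with construction after validation.
- **The numbers are assumed, and the losses may be small.** This stands. Simulation A shows no failure of the 0.75 criterion, and Simulation B shows one only for a deliberately crude score. Both use the hip fracture rate, while the main endpoint is major osteoporotic fracture. The only age grouping that the article names is five-year, and finer bands lose less. The simulations show that the loss depends on choices not yet made, which is a reason to measure it.

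**Conclusion.** The point holds in a limited form. Followed as written, the plan validates the full-weight Cox score and leaves the simplified scale without measured discrimination or calibration.

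The possible loss in C ranges from about 0.01 to 0.09 across the assumed predictors and scoring rules. Fine-grained points may cost almost nothing, while a crude scale could miss C > 0.75 although the model meets it. Which applies here cannot be told from the document. Calibration was not simulated, since it depends on how scores would be mapped to risk.

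Recruitment, sample size, data collection and endpoints are unaffected. The change is best made before the held-out third is opened. Once model performance there is known, choices about rounding and banding are no longer independent of it.

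**What to change.** In the Statistical analysis section, move construction of the simplified scale into the development step. Derive the points, the bands and the table from score to five-year risk in the development two-thirds, and lock them before the held-out third is opened.

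In that third, report for both the full model and the simplified scale the C statistic with its confidence interval, the observed/expected ratio, the calibration slope and a calibration plot. Limit any claim that the simplified scale is validated to those results. Amend the abstract's sequence to match.

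The cost is a reordering of the text and one more score through the same validation code, with no new patients or data. The scale's reported performance may come out slightly below the model's, which users should know.

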Robins et al. [19] developed a risk prediction scale for hip fracture at five years in post-menopausal women using data from the Women's Health Initiative study. The CRFs used in this scale include age, general health, weight, height, race, physical activity, personal history of fragility fracture after the age of 45, parental history of hip fracture, smoking habits, current use of corticoids and diabetes under treatment. Vazquez et al. [20] looked at a cohort in Rotterdam to evaluate the risk of hip and vertebral fracture at ten years in function of the subject's age and a risk score. The CRFs these authors examine are BMD (<19), history of fracture before the age of 50, parental history of hip fracture and the presence vertebral deformities. The usefulness of this index in our context has not yet been established, since it does not include treatment criteria, and still needs to be validated in the Spanish population.

The FRAX scale has been backed by the World Health Organization and its use has been rapidly widespread. It examines CRFs either independently or in combination with BMD to evaluate the risk of osteoporotic fracture at ten years, in men and women over the age of 50. The FRAX can be used to predict the probability of hip or other major osteoporotic fracture (clinical spine, hip, forearm or humerus). Predictors include age, sex, weight, height, history of prior fragility fracture, parental hip fracture, current smoking, long-term use of oral glucocorticoids, diagnosis of rheumatoid arthritis, secondary osteoporosis and alcohol consumption. The BMD of the hip is included as a non-clinical factor. The original study did not define criteria for treatment, but two later papers have used cost-utility analysis techniques to recommend treatment thresholds for the United Kingdom [22] and the United States [23]. These criteria, as the authors themselves point out, cannot be generalized to other countries with different fracture incidence rates and different healthcare costs.

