### Other variables

The independent variables used in this study were selected after reviewing the literature and current practice guidelines, and includes the patient's age, gender, weight and height with a calculation of the BMI, smoking habits, drinking habits, exercise habits, history of parental hip fracture, low calcium intake, untreated hypogonadism in men or women, rheumatoid arthritis, other metabolic bone diseases excluding hypogonadism, use of oral glucocorticoids, use of drugs affecting bone metabolism other than glucocorticoids, previous osteoporotic fracture, high risk of fall, prolonged immobilization, densitometric osteoporosis of the lumbar spine established through DXA (T score for L2-L4), densitometric osteoporosis of the hip established through DXA in the total hip or the femur neck (T score) and treatments for osteoporosis. The participating physicians will be trained in the management of these variables and will be given a procedures manual containing all pertinent definitions. Information about antiresorptive treatment will be collected from the GAIA system, the electronic prescription system associated with the ABUCASIS that currently covers 95% of all prescriptions dispensed in the Region. It records all the information about the drug prescribed, along with its dosage and the length of treatment.

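### The fallback for FRAX borrows weights from a model with a different predictor set, so the re-weighted FRAX can be miscalibrated; refit the FRAX items instead

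*Protocol article*

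**What the plan says.** The Statistical analysis section of the protocol article describes a sequence for FRAX. It is evaluated in the cohort. If needed, "the weights of the original scale will be used in conjunction with the incidence of osteoporotic fracture derived from our study", which keeps the FRAX weights and resets the level of risk. A second step has this trigger: "If the scale shows poor prediction capacity (statistics < 0,75), or if it is not correctly calibrated". In that case "it will be recalibrated with the weights derived from our own scale".

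The same section says where the study's own weights come from: "the most parsimonious of Cox' proportional hazards models will be applied to two-thirds of the sample". The candidates for that model are listed under Other variables. They include "high risk of fall, prolonged immobilization, densitometric osteoporosis of the lumbar spine established through DXA", and also exercise, low calcium intake and osteoporosis treatment.

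The Background section lists the FRAX items: "Predictors include age, sex, weight, height, history of prior fragility fracture, parental hip fracture, current smoking", followed by glucocorticoids, rheumatoid arthritis, secondary osteoporosis and alcohol. On bone density it adds: "The BMD of the hip is included as a non-clinical factor". Falls, immobilisation, spine densitometry, exercise, calcium and treatment are not on that list.

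**The concern.** A weight in a multivariable Cox model is the effect of one item with the other items in that model held fixed. When some of those other items are absent from the score that receives the weight, the weight no longer answers the right question. A FRAX-only score needs each FRAX item to carry its own effect plus whatever part of the absent predictors' effect travels with it. The own-scale weight has had that part removed.

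The predictor sets may also differ the other way. A FRAX item that the parsimonious model drops has no own-scale weight to import.

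At stake is specific objective 6, a FRAX recalibrated for Valencia where needed. The article links risk estimates to treatment thresholds, so errors at the two ends of the risk range matter more than the average. The step exists partly to repair poor calibration, and it could add a calibration error of its own that a comparison of overall observed and expected counts would not show.

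**Working it through.** The plan states no figure on this point, so there is none to reproduce. The check has three parts. All effect sizes and correlations are assumptions unless the article is named as their source. Overall incidence is taken as matched after the weights are imported, which is the reading most favourable to the plan.

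**1. Algebra.** Let F be the FRAX items multiplied by their own-scale weights, with standard deviation σF. Let G be the retained non-FRAX items multiplied by theirs, with standard deviation σG. Let ρ be the correlation of F and G. The hazard is proportional to exp(F + G). If F and G are jointly normal, averaging over G at a given F gives a hazard proportional to exp{(1 + ρσG/σF)F}. So

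calibration slope of the imported score = 1 + ρσG/σF.

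A slope above 1 means the imported weights are too small overall, and below 1 too large. With σF = 1:

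| ρ | σG = 0.2 | σG = 0.4 | σG = 0.6 |
|---|---|---|---|
| −0.2 | 0.96 | 0.92 | 0.88 |
| 0 | 1.00 | 1.00 | 1.00 |
| 0.2 | 1.04 | 1.08 | 1.12 |
| 0.4 | 1.08 | 1.16 | 1.24 |

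A simulation of 400,000 subjects per cell, at five-year risks of 1.5% and 5%, gave slopes within 0.01 of these. Overall observed/expected was 1.00 in every cell. Observed/expected ran from 0.88 to 1.22 in the top risk decile and from 0.53 to 1.37 in the bottom decile.

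**2. The article's planning values as a rough scale.** The sample size paragraph uses a hazard ratio of 1.33 per unit, a standard deviation of 0.75 and a squared multiple correlation of 0.10. Borrowing these for one omitted predictor:

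- σG = 0.75 × ln(1.33) = 0.75 × 0.285 = 0.214
- ρ = √0.10 = 0.316
- ρσG = 0.0676, so the slope is 1 + 0.0676/1.0 = 1.07 for σF = 1.0, and 1 + 0.0676/0.7 = 1.10 for σF = 0.7.

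The article gives that 0.10 for another purpose and does not give σF, so this is an order of magnitude only.

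**3. Named predictors.** These are simulations with assumed effects. Each left-out predictor is retained in the own scale but absent from FRAX.

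| Left out of the FRAX score | Slope | Predicted/observed, 50–59 | Predicted/observed, 80+ |
|---|---|---|---|
| Falls and immobilisation | 1.06–1.12 | 1.09–1.23 | 0.88–0.93 |
| Falls, immobilisation and treatment | about 1.01 | | |
| Treatment only | about 0.94 | | |

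A second set of runs assumed an overall risk of 4%, hazard ratios of 1.5 for falls, 1.3 for immobilisation and 0.6 for treatment. Falls and immobilisation were commoner with age, and treatment was commoner with age, in women and after a prior fracture. The slope was 1.06 without the first two and 1.03 with treatment left out as well, or 0.98 when treatment was tied more strongly to age and prior fracture. With treatment alone left out it was 0.94, with predicted/observed 0.96 at 50–59 and 1.05 at 80+.

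A slope near 1 does not show that the weights are right. In the runs that left out all three, the imported prior-fracture weight was 0.59 against 0.43–0.48 when refitted. Errors in opposite directions partly cancelled in the slope.

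**Dropped FRAX items.** Giving zero weight to a weak, independent FRAX item (standard deviation 0.2), with incidence matched, left the slope at 1.00 and the top- and bottom-decile observed/expected at 1.00. The cost is mainly discrimination.

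**The case against.** The strongest reply is that the clause is one line in a journal article. It does not say that coefficients are copied unchanged, and the full protocol may refit the FRAX items. That reading is possible, but it strains the text. The same section says that the own weights come from the parsimonious model, and weights from a separate refit of the FRAX items would not be weights of that scale. What is stated is a source for the weights, and the source is the problem.

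Other parts of the reply stand. The retained predictors are unknown: Other variables lists candidates only. If no non-FRAX predictor survives, or those that do are uncorrelated with the FRAX items, matched incidence gives a slope of about 1.00.

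A reader might infer that the re-weighted FRAX must be miscalibrated by construction, with risk always overstated in the young and understated in the oldest. The article does not support this. The error needs correlated non-FRAX predictors to be retained, and the treatment-only runs reverse the age pattern. The prior-fracture weight can also come out too large rather than too small.

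A reader might also put a T-score in the own scale and none in FRAX, which in one simulation gave a slope of 1.41. That is not a fair guide to size. The Background section lists hip bone density as a FRAX item, so only the spine score lies outside it. Densitometry is used only where an examination already exists.

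**Conclusion.** The point holds in a limited form. The stated fallback takes weights conditional on one predictor set and uses them in a score with another, and such weights are not in general correct. Whether calibration suffers, by how much and in which direction depends on which non-FRAX predictors are retained and how they correlate with the FRAX items. Slopes of about 0.94 to 1.12 are plausible under the named-predictor assumptions, and 0.88 to 1.24 over the wider grid, with larger errors in the tails than on average. All of this rests on assumed effects, on proportional hazards and on incidence being matched.

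The reach is specific objective 6, and within it a conditional second step. The main objective, the study's own scale, is not affected. It is still worth changing, because a sounder method is available from the same data at little cost.

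**What to change.** Replace the clause with wording such as:

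> If original weights combined with local incidence are inadequate, first re-estimate the calibration slope on the FRAX linear predictor. If that is still inadequate, re-estimate the coefficients of the FRAX predictor set and the baseline risk in one Cox model in the development two-thirds, and report calibration slope, observed/expected and the C statistic in the held-out third.

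Re-estimating the slope does not change how patients are ranked, so a shortfall in the C statistic leads directly to the second step.

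The cost is one extra Cox model on data already collected, with somewhat less precise coefficients for rare FRAX items. On the article's expected 180 hip fractures, two-thirds is about 120 events for the 11 clinical FRAX items listed, or about 11 per item (120/11), with about 60 events held out. That is thin for rare items in a hip fracture model, which is why the slope in the held-out third should be reported. The article expects other fractures to be more frequent, so the major fracture model should be less constrained.
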